## Source of subjects and recruitment methods

Subjects are eligible if presenting from 4 settings, as outlined above (“location of presentation”):

- Emergency departments at BWH and BWFH
- Inpatient wards at BWH and BWFH

- Patient homes of previously home hospitalized patients
- BWH and BWFH clinics
- Those meeting primary diagnosis, age, and geographic requirements will be screened by our research assistants for further enrollment (below).

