  - When surrogate consent is relied upon, assent of the subject will be a requirement for participation in the research unless the subject is incapable of giving assent due to his/her medical condition. If the individual objects to participation, s/he will not be enrolled.
  - In the case of surrogate consent, a patient must be returning to their prior level of supervision.
- For patients already on the hospital floor: Previously, we had only allowed patients who had been admitted for less than 24 hours to be home hospitalized. We now wish to expand this criterion to patients at any timepoint in their hospitalization. We believe that many patients may benefit from home hospital care, irrespective of how long they have been traditionally

hospitalized. Enrollment will proceed exactly as in the emergency department, with the exception that it will need to be assessed and reassessed daily with an inpatient team to determine the time at which the patient has a stable acute care plan that meets all of the above criteria. That is, the patient is clinically improving, has continued low probability of clinical deterioration or need for an invasive procedure, but still requires acute care.

- Subjects who do not speak English will use a short-form consent form with the assistance of a certified telephone interpreter.

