#### Covariates of Interest

| Measure                                      | Source                  | Day(s) Obtained |
|----------------------------------------------|-------------------------|-----------------|
| Age                                          | RA via EHR a | Admission       |
| Gender                                       | RA via EHR              | Admission       |
| Race/ethnicity                               | RA via patient          | Admission       |
| Primary language                             | RA via EHR              | Admission       |
| Health insurance status, public/private/none | RA via EHR              | Admission       |
| BMI                                          | RA via EHR              | Admission       |

|                                                               |                         |                |
|---------------------------------------------------------------|-------------------------|----------------|
| Comorbidities, type and #                                     | RA via EHR and H&P      | Admission      |
| Partner status                                                | RA via patient          | Admission      |
| Education                                                     | RA via patient          | Admission      |
| Zip code                                                      | RA via EHR              | Admission      |
| Employment                                                    | RA via H&P              | Admission      |
| Smoking status                                                | RA via H&P              | Admission      |
| Medications used as outpatient, #                             | RA via EHR              | Admission      |
| DNR/I code status                                             | RA via H&P              | Admission      |
| Home health aide prior to admission                           | RA via patient          | Admission      |
| Readmission risk score on discharge (HOSPITAL)                | RA via EHR              | Discharge      |
| Elective and urgent admissions in the previous year, #        | RA via EHR and patient  | Admission      |
| ED visits in the previous 6 months, #                         | RA via EHR and patient  | Admission      |
| Interqual disease-specific leveling                           | RN                      | Admission      |

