## Statistical methods

### *Home hospital vs traditional hospital*

#### *Quantitative*

We plan to form 3 different control groups (with groups listed in order of preference):

1. Patients who were deemed eligible for home hospital, but the service was full (and they were not enrolled subsequently if the service was no longer full);
2. Patients who were deemed eligible for home hospital, but lived outside of the 7.5-mile catchment area; and
3. Patients who were admitted to the hospital.

For each control group, we will use propensity score weighting, adjusting for covariates of interest (see table above), baseline functional status, and DRG. We will be cognizant of over-adjustment depending on our final sample size for each group above. If possible, we will use only group 1 above, as it is the strongest. If we have insufficient control group sample size, we may choose to combine groups 1 and 2 above.

The primary outcome (hospitalization cost) will be assessed using a generalized linear model assuming a gamma distribution with a log link. We will use a multivariable regression approach for secondary

outcomes, using logistic regression for binary outcomes and non-transformed linear regression for normally distributed continuous outcomes as appropriate.

We *a priori* plan to perform a subgroup analysis that does not involve any outlier participants, should this occur. We also *a priori* plan subgroup analyses by diagnosis, by age group, by disposition, by location of admission (e.g., ED, floor, clinic, and home), and by daily activity level. We also *a priori* plan to analyze our outcomes with means, but also with median and interquartile ranges, which are less subject to outlier effects. We may choose to employ non-parametric tests of significance should our data be nonparametric.

We *a priori* plan to adjust our secondary analyses using the Benjamini-Hochberg method. We *a priori* choose a false-discovery rate of 0.20.

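### Location of presentation is left out of the propensity variables, so the pooled home-versus-hospital cost estimate may be confounded by route of entry, in either direction

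*Protocol*

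**What the plan says.** Under Source of subjects and recruitment methods, the protocol states "Subjects are eligible if presenting from 4 settings, as outlined above": emergency departments, inpatient wards, clinics, and "Patient homes of previously home hospitalized patients".

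The selection rules differ by route (Inclusion/exclusion criteria, location of presentation; Methods of enrollment):

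- **Floor:** accepted at any point in the stay, once "the patient is clinically improving, has continued low probability of clinical deterioration or need for an invasive procedure, but still requires acute care".
- **Clinic:** the referrer must know the patient well and be sure of diagnosis and management.
- **Home:** only patients with an earlier home hospitalization.
- **All non-ED routes:** the full inclusion and exclusion criteria still apply. Clinic and home entrants need the same warranted work-up as in the emergency department or on the ward.

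For the primary cost comparison, Statistical methods (Home hospital vs traditional hospital, Quantitative) states: "For each control group, we will use propensity score weighting, adjusting for covariates of interest (see table above), baseline functional status, and DRG". The table meant is Covariates of Interest. It includes "ED visits in the previous 6 months" and "Interqual disease-specific leveling", but no row for where the current episode began. In this comparison, location is used only for a subgroup analysis, "by location of admission (e.g., ED, floor, clinic, and home".

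Three control groups are ranked: (1) eligible patients for whom the service was full and who were not enrolled later; (2) eligible patients living outside the catchment area; (3) patients admitted to the hospital. Group 1 alone is to be used if possible.

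**The concern.** A propensity-weighted comparison needs the variables that drive both entry to treatment and the outcome. Route of entry is a pre-treatment variable, and the protocol's own rules tie it to selection. It can plausibly bear on cost as well: a floor entrant has already passed the start of the illness and is improving, while a home entrant is by definition a repeat user of the service.

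If the weighted home and control groups hold different shares of each route, the pooled cost ratio mixes the effect of home care with the difference between routes. The subgroup analysis would reveal differences between routes but leaves the headline figure uncorrected. At stake is the primary result, which is read against a target of a 20% cost reduction.

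**Working it through.** **Step 1. Is location among the weighting variables?** The stated set has three parts.

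- *Covariates of Interest table:* demographic and social items, comorbidities, medications, prior admissions and ED visits, InterQual level, frailty, cognition, literacy, readmission score. There is no row for location of presentation. The ED item counts past visits and does not say whether this episode began in the ED.
- *Baseline functional status:* not location.
- *DRG:* diagnosis grouping, not location.

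So location is absent. Early transfer to home hospital vs traditional hospital adds one variable, for patients first missed because the census was full and taken home later. That variable belongs to a separate analysis and is not location of presentation. The remote-versus-in-person section expressly allows further covariates if groups differ at baseline. The home-versus-hospital section has no such allowance and warns of over-adjustment.

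**Step 2. Do the control groups balance route by design?**

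- *Group 1* is defined by eligibility and not limited to one route, so it can contain all four. It drops patients who were blocked by the census and enrolled later. A ward patient enrolled later must be stable and improving, so such patients can move from the control pool to the home group.
- *Group 2* is also defined by eligibility. It should hold few home-route patients, because that route needs an earlier home hospitalization and these patients live outside the catchment.
- *Group 3* carries no eligibility or route condition.

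Exposure therefore rises from group 1 to group 3.

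**Step 3. How large could it be?** The protocol states no route mix and no cost by route, so there is no figure to reproduce and what follows is illustration only. Let p1 and p0 be the shares entering by a non-ED route in the weighted home and control groups, and r the cost of that route relative to the ED route. Suppose the effect of home care is the same on every route and the other covariates capture none of the route difference. Then

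apparent cost ratio = true ratio × (1 − p1 + p1·r) / (1 − p0 + p0·r).

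With a true ratio of 1 (no effect) and assumed inputs:

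| p1 | p0 | r = 0.6 | r = 0.8 | r = 1.25 | r = 1.5 |
|---|---|---|---|---|---|
| 0.10 | 0.10 | 1.000 | 1.000 | 1.000 | 1.000 |
| 0.30 | 0.10 | 0.917 | 0.959 | 1.049 | 1.095 |
| 0.40 | 0.10 | 0.875 | 0.939 | 1.073 | 1.143 |

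Example: p1 = 0.30, p0 = 0.10, r = 0.6 gives (0.70 + 0.18) / (0.90 + 0.06) = 0.88 / 0.96 = 0.917.

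With a true ratio of 0.80, the two extremes in the last row become 0.80 × 0.875 = 0.700 and 0.80 × 1.143 = 0.914.

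**Step 4. Is the sign known?** It is not. The Cost table takes episode cost from home hospital accounting and does not say whether a floor entrant's earlier ward days count. If they do not count, those episodes are cut short and look cheap. If they do, those episodes may look expensive.

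**The case against.** The strongest defence is the design of the controls. Group 1 is preferred, is defined by eligibility, and admits every route. A ward patient judged eligible but turned away met the same criteria as one taken home. Group 2 rests on eligibility too. The weights also carry InterQual level, comorbidity, prior use, frailty, functional status and DRG, which may absorb part of any route difference. Results by location are planned, and early transfer has its own study. This stands as a reason why the bias may be small with group 1. It does not remove the problem: later-enrolled patients are taken out of group 1, its use is only conditional, and none of the listed covariates states how a ward patient was progressing at transfer.

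A reader might infer that route differences will be booked as home hospital savings, because floor entrants come after the costly first days and clinic or home entrants avoid the ED work-up. The documents do not support that. They give no mix or cost by route, they leave the handling of earlier ward days open, and they require the same warranted work-up on the clinic and home routes. Nor can it be said that clinic entrants have no hospital counterpart: the protocol's own example is a patient who would otherwise be admitted directly, and such a patient turned away for census is a control.

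It can also be argued that, for home-route patients, avoiding the ED is part of what the service does and so is not confounding. That is a fair question about the estimand. Without controls from that route, however, the data cannot answer it.

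**Conclusion.** The point holds in a limited form. Location of presentation is known before treatment, is tied to selection by the protocol's own rules, and is missing from a stated list of weighting variables. The pooled primary cost estimate may be confounded by route. The direction is open, and the size cannot be derived from the documents. The range 0.875 to 1.143 rests wholly on assumed mixes and cost ratios, and on no help from the other covariates. It shows only that an imbalance of that order would matter against a 20% target. With equal mixes the bias is nil. The protocol should be changed here because the remedy is cheap, not because a particular bias has been shown.

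**What to change.** In the Quantitative section for home hospital versus traditional hospital, add location of presentation to the propensity model, or match exactly on it before weighting, and add a matching row to Covariates of Interest. For controls, define it at the time eligibility was assessed or the admission decision was made; otherwise every hospital control ends up classed as a floor patient.

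Report overlap and balance by route for whichever control group is used. Leave any route without comparable controls out of the pooled primary estimate and describe it in the planned location subgroup. A comparison limited to patients whose admission decision was made in the ED can serve as a sensitivity analysis. As the primary analysis it would change the estimand and shrink the control pool, which the protocol already expects may be short.

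The cost is a change of analysis wording and one variable that the planned subgroup already needs. The downside is a somewhat smaller primary set if a route lacks controls, with the estimate then applying only to routes that have them.

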### *Qualitative*

During and after the intervention period, we will interview a sample of patients and caregivers 7-30 days after discharge (irrespective of their experimental arm) regarding their opinions of their hospitalization. We will use this data to both iteratively improve home hospital and make detailed qualitative comparisons between home hospital and usual care.

In all cases, we will use semi-structured interview guides to ask questions regarding the hospitalization experience. Interviews will be recorded, transcribed, and then analyzed using NVivo qualitative analysis software. Drs. [name] and [name] will perform dual coding of all themes, and all differences will be discussed and reconciled. We will use an *a priori* analytic framework based on the Systems Engineering Initiative for Patient Safety Model (SEIPS), which describes processes and outcomes as products of the interactions among patients, technology and tools, the health care organization, the tasks at hand, and the physical environment.

### *Remote vs In-Person Physician Care*

In a randomized controlled non-inferiority trial, we will test an in-person daily physician visit (“in-person care;” control) vs a daily physician visit conducted remotely via video facilitated by a care team member (“remote care;” intervention) for acutely ill patients who are home hospitalized. The primary outcome (dependent variable) is number of adverse events during the acute episode of care (see “Summarizing Adverse Events” table below). The primary predictor (independent variable) is study arm (in-person care vs remote care). We will assess the non-inferiority of the primary outcome with a generalized linear model using Poisson distribution, given the primary outcome is count data. Although we have multiple covariates of interest, we are cognizant of over adjustment. We plan to adjust for age, gender, race/ethnicity, PRISMA-7, education, and HOSPITAL score). We may include additional covariates if groups have significant differences at baseline.

Because patients in the intervention arm will receive at least some of their intervention through a “change agent” (in this case, a Home Hospital team) shared with other participants, we need to account for this in the analysis. We will therefore cluster by Home Hospital physician using general estimating equations.

Other outcomes will be analyzed in a similar manner, using Poisson regression for other “count” outcomes (e.g., number of new or worsening signs or symptoms per patient, days at home since discharge), multivariable logistic regression for binary outcomes (e.g., 30-day readmission, ED visit, PCP

appointment within 7 or 14 days, ability to meet physical milestones after discharge), non-transformed linear regression for normally distributed continuous outcomes (e.g., quality of life scores), log-transformed linear regression for skewed continuous outcomes (e.g., cost), and Cox proportional hazards for time to event outcomes (e.g., time to readmission, time to ED visit). We will use multiple imputation for covariates where data are missing for more than 2% of patients. Lastly, we will perform a limited number of subgroup analyses to determine whether the intervention is more effective in certain patient populations than in others (i.e., effect modification), targeting inadequate health literacy and living alone, for example. We will use interaction terms (e.g., intervention\*characteristic) to determine the statistical significance of effect modification.

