**Patient Functional Status and Quality of Life**

| Measure        | Source         | Day(s) Obtained                |
|----------------|----------------|--------------------------------|
| EuroQol -5D-5L | RA via patient | Admission, discharge, +30      |
| SF-1           | RA via patient | -30, admission, discharge, +30 |

|                                                                                                     |                |                                |
|-----------------------------------------------------------------------------------------------------|----------------|--------------------------------|
| Activities of daily living: admission to discharge; admission to 30-day post-discharge              | RA via patient | -30, admission, discharge, +30 |
| Instrumental activities of daily living: admission to discharge; admission to 30-day post-discharge | RA via patient | -30, admission, discharge, +30 |
| Patient Health Questionnaire-2                                                                      | RA via patient | Admission, discharge, +30      |
| PROMIS Emotional Support Short Form 4a                                                              | RA via patient | Admission, discharge, +30      |
| Days at home since discharge                                                                        | RA via patient | +30                            |
| Milestones                                                                                   |                |                                |
| Walk around ward/home                                                                               | RA via RN      | Discharge                      |
| Get to (non-commode) bathroom                                                                       | RA via RN      | Discharge                      |
| Walk 1 flight of stairs                                                                             | RA via RN      | Discharge                      |
| Visit with friends/family                                                                           | RA via patient | Discharge                      |
| Walk outside around my home                                                                         | RA via patient | +30                            |
| Go shopping                                                                                         | RA via patient | +30                            |

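### Remote vs in-person RCT: the admission score is collected for quality-of-life, mood and function outcomes but not prespecified as a covariate, at some cost in precision for outcomes outside the named endpoints

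*Protocol*

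**What the plan says.** The covariates for the RCT are set in Statistical methods, under Remote vs In-Person Physician Care: "We plan to adjust for age, gender, race/ethnicity, PRISMA-7", followed by education and the HOSPITAL readmission score. The rule for extending the list is "We may include additional covariates if groups have significant differences at baseline". The section then turns from the primary outcome to the rest: "Other outcomes will be analyzed in a similar manner", including "non-transformed linear regression for normally distributed continuous outcomes (e.g., quality of life scores").

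The table Patient Functional Status and Quality of Life shows what is measured and when. The EQ-5D-5L row reads "EuroQol -5D-5L | RA via patient | Admission, discharge, +30". The "Patient Health Questionnaire-2" and the PROMIS Emotional Support form follow the same schedule. SF-1, ADL and IADL are taken at those times and also for 30 days before admission. The ADL row is worded as a change, "Activities of daily living: admission to discharge; admission to 30-day post-discharge", and the IADL row likewise.

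For the separate comparison of home with traditional hospital, the Quantitative section plans propensity weighting "adjusting for covariates of interest (see table above), baseline functional status, and DRG".

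**The concern.** The admission score of an instrument is usually among the better predictors of its later score. The protocol pays for that measurement in six instruments and then does not commit to using it as a covariate in the randomised comparison.

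The one route by which it could enter is a significant baseline difference. In a randomised trial such differences arise by chance, and a significance test does not show whether a covariate predicts the outcome. A strongly prognostic score that is balanced stays out, although including it would narrow the interval. A weakly prognostic one that happens to be imbalanced may come in. The covariate set then depends on the data.

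At stake are wider confidence intervals than necessary for these outcomes, and estimates that carry whatever chance imbalance in the admission score falls short of significance.

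**Working it through.** **What can be reproduced.** The protocol gives no power, effect size, SD or admission-to-follow-up correlation for any of these outcomes, so there is no figure of its own to reproduce. The RCT sizes in the power analysis (105 per arm before clustering, 130 after) are set for adverse events and are used below only for scale.

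**Assumptions.** Correlation ρ between admission and follow-up score, varied from 0.3 to 0.7. Equal variances at the two times and a linear model. Base power 80% for the follow-up score without the admission score. z = 1.96 for the test and 0.8416 for 80% power, which sum to 2.8016. The six listed covariates and clustering by physician are ignored at first.

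**1. Follow-up score with and without the admission score.** Adjustment multiplies the residual variance by (1 − ρ²), so

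power = Φ(2.8016/√(1 − ρ²) − 1.96).

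| ρ | √(1 − ρ²) | Power with admission score | Gain over 80% |
|---|---|---|---|
| 0.3 | 0.954 | 83.6% | about 4 points |
| 0.4 | 0.917 | 86.4% | about 6 points |
| 0.5 | 0.866 | 89.9% | about 10 points |
| 0.6 | 0.800 | 93.8% | about 14 points |
| 0.7 | 0.714 | 97.5% | about 18 points |

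The gain also depends on the assumed base power. At ρ = 0.5, a base of 50% rises to 61.9%, 70% to 81.8% and 90% to 96.3%.

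**2. The same gain as a detectable difference.** At 130 per arm, ignoring clustering, 80% power corresponds to 2.8016 × √(2/130) = 0.347 SD. With the admission score at ρ = 0.5 it is 0.347 × √0.75 = 0.301 SD.

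**3. Allowing for the covariates already listed.** Age and PRISMA-7, for example, will carry part of the same information. Suppose the six explain 5–15% of the outcome variance and adding the admission score brings this to 25–35% (assumptions again). Then

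power = Φ(2.8016 × √[(1 − R²listed)/(1 − R²with admission)] − 1.96).

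This runs from 84.7% (15% to 25%) to 92.3% (5% to 35%), a gain of about 5 to 12 points.

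**4. ADL and IADL read as changes from admission.** A change score has variance 2(1 − ρ) relative to the follow-up score, so its power on the scale of step 1 is Φ(2.8016/√[2(1 − ρ)] − 1.96).

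| ρ | Change score alone | Baseline-adjusted |
|---|---|---|
| 0.3 | 65.8% | 83.6% |
| 0.5 | 80.0% | 89.9% |
| 0.7 | 95.1% | 97.5% |

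The variance ratio of adjusted to change analysis is (1 − ρ²)/[2(1 − ρ)] = (1 + ρ)/2, which never exceeds 1. Baseline adjustment is therefore at least as efficient at every ρ, and the difference shrinks as ρ rises.

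**5. Where these outcomes stand.** In the Study endpoints table the RCT's primary is the number of adverse events. Its secondaries are unplanned readmission, the Picker questionnaire and a global experience score. The patient-experience measures are collected only at +30, so they have no admission value to adjust for. No named RCT endpoint is affected.

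**The case against.** The best case against the point is that it concerns detail. The covariate sentence sits in the paragraph on the primary outcome and states a plan, not a closed list. The clause on other outcomes introduces a set of model families and does not say that exactly these six covariates apply to each. Outcome-specific covariates for outcomes outside the named endpoints are ordinary analysis-plan material. The protocol also voices a concern about over-adjustment. Much of this stands, and it is why the point is minor. What remains is that the protocol is not silent: it states a list, carries the approach over and gives a rule for additions, and that rule is the wrong one. Over-adjustment is not a serious worry for one extra covariate in a linear model with 210 to 260 patients.

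Four stronger readings are tempting and are not supported:

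- **That the trial gives up about 10 points of power.** That figure needs ρ = 0.5 and 80% base power, neither of which is in the protocol, and it ignores the six covariates already planned.
- **That the admission value goes unused for function.** ADL and IADL are worded as changes from admission, so it is already part of the outcome. At high ρ a change score does nearly as well as adjustment.
- **That a stated aim of the RCT suffers.** The function and quality-of-life aim under Secondary Aims refers to adults who would otherwise be admitted to hospital, that is, the home versus traditional hospital comparison. There, baseline functional status is already in the adjustment.
- **That the estimates are biased.** Randomisation keeps the comparison valid without the covariate.

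Nor is there any calculation to support adding the 30-days-before-admission scores as further covariates.

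**Conclusion.** The point holds as a free improvement. For the RCT, the admission score of EQ-5D-5L, SF-1, PHQ-2, PROMIS Emotional Support, ADL and IADL is collected but not prespecified as a covariate, and its entry is tied to a baseline significance test.

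The size is conditional: about 4 to 18 points of power for ρ from 0.3 to 0.7 starting from an assumed 80%, and somewhat less once the listed covariates are credited. For ADL and IADL the relevant contrast is with a change score, and the advantage there is large at low ρ and small at high ρ. All figures assume a linear model and equal variances over time, and ignore clustering. They are a rougher guide for very short scales such as SF-1 and PHQ-2. They also assume that the admission score is taken before the arms can diverge.

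**What to change.** Add one sentence to the paragraph on other outcomes under Remote vs In-Person Physician Care. For EQ-5D-5L, SF-1, PHQ-2, PROMIS Emotional Support, ADL and IADL, the outcome is the discharge or +30 score, and the model includes the admission score of the same instrument whatever the baseline balance. Missing admission scores come under the multiple imputation of covariates that the section already plans. Leave the 30-days-before-admission scores out of this change.

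The cost is one sentence and one covariate per model. There are no new data, visits or patients, and the primary analysis is unchanged.
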